### The intervention

Community leaders are oriented to the 3-Step Model by the research team and establish a coordinating committee to oversee implementation of the *Mzake* intervention using the 3-Step Model. We use the procedures and materials that were developed for the *Mzake* efficacy study. Leader training is highly interactive with extensive practice and feedback so that leaders learn how to facilitate the group rather than lecturing, which is the usual learning modality [36, 37]. Because the capacity to train new leaders needs to be established locally, we plan to establish a group of health worker volunteers who can serve as trainers. Interactive assistance is provided during implementation of *Mzake* using the Model. This assistance is designed to gradually decrease as communities build capacity for independent implementation. To support independence, each site also receives a Toolkit which includes the Coordinating Committee Implementation Guide, Benchmarks Checklist, the Peer Leader Training Guide and the Adult and Youth *Mzake ndi Mzake* Manuals, and the physical materials required for *Mzake* sessions. During the pilot we made a training video showing how to facilitate a group using examples from actual group sessions. Prior research has found that implementation proceeds more quickly with technical assistance, although the Toolkit alone may be enough for some sites [24].

### Measures

This mixed-methods evaluation uses multiple types of data from different sources. Table 1 below summarizes the data sources and measures. Most materials are already translated, but new materials are translated using a team approach throughout the study. After initial translations and back-translations, a translation team (bilingual nurse, academic, and lay persons) reach consensus regarding differences, ensuring that the materials are accurate, comprehensible and conceptually equivalent [38–41].

**Table 1 Tab1:** Evaluation measures

Aim	Measures
1. Implementation progress	
Benchmarks	26 yes/no items (1 point for each done) measuring implementation progress at each site. Numeric summaries are also recorded for peer leaders trained, 7-session peer groups and boosters held (# completed, # of adult and youth participants). Scored every 6 months. Summaries for each community and the total are presented to the community and district leaders and integrated with related local health outcome data (e.g., # of HIV tests provided, % of pregnant women tested) routinely collected and provided by the District Health Officer.
2. Implementation patterns and process	
Peer group fidelity ratings	• Structured fidelity ratings by the Research team (trained to an inter-rater reliability of 0.85) [37]. At least one of the early sessions of all peer leaders plus randomly selected groups thereafter is observed. • Peer leaders’ self-assessments and attendance sheets
Observation notes on meetings	Study notes by the research team (semi-structured observations of all meetings attended) documenting type of meeting or observation, date, site, and discussion related to successes, challenges, if problem was solved; and personal interactions
Annual focus group & Individual Interviews	7–12 focus group interviews with district and community implementation partners and 8–12 individual interviews with implementation partners including local “champions” and unsupportive individuals. Coded to identify successes, problems/barriers/ solutions, and appraisal of support and technical assistance
3. Effectiveness for Participants	
Survey	• Demographics (e.g., Age; education; current partner status) • Program time/dose: Date of last session attended; # of sessions attended • Comprehensive HIV-related Knowledge: (5 HIV & 4 PMTCT items [35]) • Safer sex Practices over the last 2 months [10] (Primary Outcome) (a) *Self-efficacy scale* (4 items, # discussed: HIV prevention, condom use, being faithful, HIV test with partner; responses very, somewhat, not confident, range 3–12); (b) Partner communication index (4 yes/no items, # discussed: HIV prevention, condom use, being faithful, HIV test with partner); (c) If abstained; d) If sexually active, condom use (always, sometimes, never); • Sexual Risk Index [10] (had unprotected sex, more than one partner, sex for money, sex while drinking, sex with a stranger; 5 items, # Yes) • If used a condom at last sexual relations [35] • If not sexually active at baseline, whether sexual debut occurred (youth only) • HIV Test (Primary Outcome): If had HIV test in last year, yes-no; if yes, whether tested with partner [10]
STIs	• Original Plan: Tests for clinical and sub-clinical gonorrhea, chlamydia, and syphilis using minimally invasive rapid tests appropriate for use in a community setting without electricity or access to laboratory or examination facilities. This plan had to be modified because tests were withdrawn from the market and/or found to be unreliable in new research [45, 46]. • Revised Plan: Detailed interview regarding STI symptoms experienced in the last week and in last 6 months (with referral for clinic follow-up when indicated)
4. Integration of patterns with effectiveness and sustainability	
All above data	Within and cross-case matrices: implementation patterns and relationship to progress benchmarks, effectiveness, if sustained program

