**Methods:**

Three communities in southern Malawi begin implementation in randomly-assigned order using a stepped wedge design. Our evaluation sample size of 144 adults and 144 youth per community provides sufficient power to examine primary outcomes of condom use and HIV testing. Prior to any implementation, the first participants in all three communities are recruited and complete the Wave 1 baseline survey. Waves 2–4 surveys occur after each community completes roll-out. Each community follows the model’s three steps. During Prepare, the community develops a plan and trains peer group leaders. During Roll-Out, peer leaders offer the program. During Sustain, the community makes and carries out plans to continue and expand the program and ultimately obtain local funding. We evaluate degree of implementation success (Aim 1) using the community’s benchmark scores (e.g, # of peer groups held). We assess implementation process and factors related to success (Aim 2) using repeated interviews and observations, benchmarks from Aim 1 and fidelity assessments. We assess effectiveness of the peer group intervention when delivered by communities (Aim 3) using multi-level regression models to analyze data from repeated surveys. Finally, we use mixed methods analyses of all data to assess feasibility, acceptability and sustainability (Aim 4).

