### Setting and sample

The study takes place in Phalombe District in southern Malawi. The district has a population of nearly 350,000 [30]. In consultation with District leaders, we identified one sub-district area as the most appropriate place to test the 3-step model. This area is the largest in the district; a third of the district’s population resides there. The leaders in that area selected three communities as sites for implementation.

The sample includes both the implementation partners described above, who share their perspectives on the implementation process (Aim 2), and community members, who participate in the intervention (Aim 1) and its effectiveness evaluation (Aim 3). District level leaders from government, the health sector and traditional leaders collaborate for implementation and are included in qualitative evaluation. Implementation partners in each of the three communities include a coordinating committee that will oversee implementation and the trained peer leaders. Eligibility criteria for implementation partners include being in the designated role and willingness to participate.

The community member participants include adults and youth (ages 13–19) who take part in the 7-session peer group intervention. The first 144 adults and 144 youth in each community participate in both the peer group intervention and the repeated effectiveness surveys. Participants also provide information for the process evaluation during periodic group session observations, focus groups and repeated individual interviews. Eligibility criteria for community participants include residing in the designated community and, for youth, being within the designated age range and having parental permission to participate if under age 18. We subsequently increased the number of youth recruited, because they are more likely to move away over time.

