#### Power analysis, Aim 2 effectiveness

We performed a power analysis for the stepped wedge effectiveness component to determine sample size. Conventional power calculation programs are not able to consider both the intra-class correlation (ICC) for the intervention clusters, and the ICC for repeated measures of individuals over time. Therefore, we performed 1000 simulations using the stepped wedge design, for both continuous outcomes (analyzed using mixed-effects regression) and binary outcome (analyzed using mixed-effects logistic regression) [31, 32]. We conservatively set cluster-level ICC to be 0.10, based on two previous community or classroom studies that found an ICC of 0.05 [33, 34]. Individual-level ICC was set to range from 0.2 to 0.4, as is typical for correlations between repeated measurements of an individual. We set retention rates at 85, 80, and 75% at waves 2 through 4, a conservative estimate given our prior study with 80% retention at 18 months. Expected effect sizes (0.10 to 0.20 for continuous outcomes; odds ratios ranging from 1.2 to 2.2 for dichotomous outcomes) were based on significant outcomes in our previous efficacy study [10, 11] or, for comprehensive HIV knowledge and sexually transmitted infection (STI) prevalence, a 2010 national survey [35]. With 80% statistical power, the sample of 432 persons (youth or adults) with retention rates of 75% at the last wave, supported a minimum detectable effect size of 0.13 for continuous outcome variables, and a minimum detectable odds ratio of size 1.36. Thus, we have sufficient power to detect all expected intervention effects for outcome variables for adults and youth separately.

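### Condom use is collected only from people sexually active at each wave, so its before-after contrast can be biased by who is active, and the detectable odds ratio of 1.36 on 432 does not apply to it

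*Protocol article*

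**What the plan says.** The abstract states that 144 adults and 144 youth per community "provides sufficient power to examine primary outcomes of condom use and HIV testing".

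Table 1 places condom use under the heading "Safer sex Practices over the last 2 months [10] (Primary Outcome"), where component (c) is whether the person abstained and component (d) reads "If sexually active, condom use (always, sometimes, never"). Abstention therefore carries the same primary label, and condom use is asked only of those who did not abstain. The table also lists, as a separate item, "If not sexually active at baseline, whether sexual debut occurred (youth only").

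Under Setting and sample, youth are aged 13 to 19, and sexual activity is not an eligibility criterion for either age group.

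The power section reports, at 80% power, that "the sample of 432 persons (youth or adults) with retention rates of 75% at the last wave" supports a detectable odds ratio of 1.36. It concludes that power is sufficient for all expected effects in adults and youth separately. The expected odds ratios run from 1.2 to 2.2. Retention of 85%, 80% and 75% at waves 2 to 4 is the only reduction in numbers.

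The Aim 3 analysis section specifies mixed logistic regression with random individual and peer-group effects. It gives no rule for person-waves without sexual activity.

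**The concern.** There are two linked problems.

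First, the comparison. With a two-month window, the people who have a condom-use value are redefined at every wave. If roll-out leads some people to abstain, or delays debut in youth, those contributing after roll-out differ from those contributing before it because of the intervention. Randomising the order of the sites does not protect a contrast within a subgroup formed after the intervention starts. A gain in abstinence could appear as better or worse condom use, depending on who abstains.

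Second, the power statement. A detectable odds ratio worked out on everyone enrolled is applied to an outcome that some of them will not have. Youth are the more exposed group: the age range starts at 13, and tracking debut presupposes that some are inactive at baseline.

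**Working it through.** **1. The plan's own figure.** The article does not give alpha, the control rate or the time terms of the simulation, so 1.36 cannot be reproduced from the text alone. I used a closed-form calculation for three sites and four waves: 144 per site, cluster ICC 0.10, retention 100/85/80/75%, and assumed two-sided 0.05, a control rate of 0.25 and no wave effects. At individual ICC 0.2, 0.3 and 0.4 it gives:

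- detectable effect sizes of 0.135, 0.126 and 0.115 (stated 0.13);
- detectable odds ratios of 1.37, 1.34 and 1.31 (stated 1.36).

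The stated values therefore fit the full 432 with retention losses only. Adding wave effects raises the odds ratio on all 432 to 1.58–1.72. That is a separate matter and is not used below.

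**2. Restricting to the active.** Inputs: 1.36 (power section) and the active fraction f (assumed). If information is proportional to the number of active people:

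- detectable OR = exp(ln 1.36 / √f), with ln 1.36 = 0.3075;
- power at OR 1.36 = Φ(2.80·√f − 1.96).

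| f (assumed) | Persons (432·f) | Detectable OR | Power at OR 1.36 |
|---|---|---|---|
| 1.0 | 432 | 1.36 | 80% |
| 0.8 | 346 | 1.41 | 71% |
| 0.5 | 216 | 1.54 | 51% |
| 0.3 | 130 | 1.75 | 34% |
| 0.2 | 86 | 1.99 | 24% |

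The full closed form, without wave effects and with individual ICC 0.2, agrees: 1.55 at f = 0.5 and 1.77 at f = 0.3. If activity comes and goes between waves, these become 1.59 and 1.84.

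**3. Against the earlier effect.** The Background gives condom use in youth as 70% v 49%: OR = (0.70/0.30)/(0.49/0.51) = 2.43. In adults, 25% v 12% gives (0.25/0.75)/(0.12/0.88) = 2.44. On the scaling above, 80% power at these odds ratios needs f = (ln 1.36 / ln OR)², about 0.12, or roughly 52 persons.

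**4. Selection with no change in condom use: outer limits.** Take 100 active youth, 49 of them condom users (the earlier youth control rate; its denominator is not stated).

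- 10 abstain: 49/90 = 54.4% if all were non-users (OR 51/41 = 1.24); 39/90 = 43.3% if all were users (OR 39/49 = 0.80).
- 20 abstain: 49/80 = 61.3% (OR 51/31 = 1.65) or 29/80 = 36.3% (OR 29/49 = 0.59).

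**5. A milder case.** Assume 60% are active, half using condoms with probability 0.7 and half with 0.3, and activity falls to 50%.

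- All new abstainers from the riskier half: (0.30×0.7 + 0.20×0.3)/0.50 = 0.54, OR 0.54/0.46 = 1.17.
- All from the safer half: 0.46, OR 0.85.

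**6. Does the planned model remove it?** A simulation used the stated design and retention, wave and site effects, a random person intercept (individual ICC 0.3), baseline use near 50%, a true OR of 1.0, 3,000 people per site to isolate bias, and an assumed 20% of active people abstaining after roll-out. With abstention unrelated to risk, the fitted OR was 0.97–1.02. With abstention related to a person's stable risk, it was 1.17–1.19 when riskier people abstained and 0.77–0.88 when safer people did. The size depends on how strong the selection is assumed to be; the result that matters is that the random intercept leaves a bias of either sign.

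**The case against.** Much of the opposing case stands.

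- **Abstention is not hidden.** It shares the primary label, so the two items can be read together. Yet the abstract names condom use alone as the powered outcome.
- **Table 1 lists questionnaire items, not analysis populations.** No text says abstainers are dropped, and an analysis plan may code them. But a person with no condom-use value cannot enter the model without such a coding, and the article's power claim is made without one.
- **No effect on abstinence or debut is reported.** The Background gives effects on condom use and testing only. A reader might infer that the intervention does change who is active; the documents support only that it may.
- **Power may be ample.** A reader might infer that condom use is underpowered. The documents do not show this: even at 20% active the detectable odds ratio of 1.99 lies below both the earlier 2.4 and the upper expected value of 2.2.
- **The limits in step 4 are extremes.** They need every new abstainer to be of one kind, and they compare crude proportions, whereas the plan follows one cohort with random individual effects.
- **A near-equivalent item exists.** The Sexual Risk Index already asks about unprotected sex. Replacing a primary outcome in a registered trial, with two of three communities already rolling out, would be a substantial change. This argues for adding an analysis and against replacing the outcome.

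The later increase in youth recruitment does not answer the point: it is not quantified, and the reason given is that youth move away.

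**Conclusion.** The point holds in this form. Condom use is collected conditionally on recent sexual activity, which the programme may alter, so the conditional contrast can be biased in either direction and the planned random effects only lessen this. In the partial-selection example the spurious odds ratio is 0.85 or 1.17; how far real data would move depends on who becomes or stays active, which the article cannot tell us.

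The detectable odds ratio of 1.36 belongs to outcomes measured on all 432 per age group. For condom use it is about 1.41 to 1.99 over an assumed 80% to 20% active, so expected effects between 1.36 and that value lose the stated 80% power. The figures rest on the assumed active fraction, on information proportional to the number active, and on the stated 1.36 as the anchor. They show that the sufficiency statement is unqualified where it should not be. They do not show that the trial would miss an effect as large as the earlier one.

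**What to change.** 1. Restate the detectable odds ratio for condom use, separately for adults and youth, on the expected number sexually active, giving the assumed fraction and its source. Limit the sufficient-power sentence to match.
2. Keep condom use as the declared primary outcome, but label it as conditional on sexual activity in the past two months.
3. Pre-specify beside it an all-participant analysis of any unprotected sex in the same window: no if the person abstained or always used a condom, yes otherwise. Derive it from items (c) and (d), or use the existing Sexual Risk Index item. Report abstention next to it by wave and condition, so that a shift in who is active can be seen.

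No new data are needed. The costs are one more analysis, an added outcome that mixes abstinence with condom use and is less directly comparable with the efficacy study, and a less favourable stated detectable odds ratio.

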### Implementation procedures

#### District-level preparation (months 1–8)

We first obtain ethical approval at both universities, hire staff, establish an office and train the research team, including training or updating in ethical conduct of research and a confidentiality pledge. We then reconfirm our collaboration with district partners and community leaders, make plans and orient them to the intervention. The district nursing officer identifies up to 12 health workers who attend a Training of Trainers workshop led by the Co-Investigators. Training ends with a pilot, where health workers practice conducting peer groups with community volunteers. Sessions are videotaped and used to develop a training video to illustrate effective group facilitation techniques.

#### Implementation at 3 sites

We test the 3-Step Model in the 3 sites sequentially, with the order of introduction at each site randomly assigned during a public meeting. The same sequence of implementation steps and activities occurs at all sites.

During the *Prepare* step (2 months), community leaders are oriented to the program and form a site coordinating committee comprised of respected adults active in community affairs. The committee is oriented to the 3-Step Model and *Mzake.* They learn about the benchmarks which they use to develop a plan and evaluate progress every 6 months (Table 1). After making a community implementation plan, they recruit volunteers to become peer leaders. The volunteers are trained to deliver *Mzake,* maintain group records and complete a brief self-evaluation of fidelity. *The primary capacities built during this period are conceptual understanding of the* 3-Step Model *and Mzake; planning and coordination for the coordinating committee and peer group leadership skills for peer leaders.*

During *Roll-Out* (8 months), *Mzake* is introduced to community members at village meetings and those who are interested sign up to be in the peer groups and complete informed consent. The first 144 participants must also agree to complete the repeated effectiveness surveys. Peer leaders conduct the first round of 12 groups with adults, then reflect on their experiences with the coordinating committee and make any modifications. Because talking about sexuality with youth is a sensitive topic in Malawi, the leaders obtain experience and confidence with adult groups and then the same peer leaders offer 12 groups with youth. During both adult and youth groups, the research team rates fidelity and provides supportive coaching for each pair of leaders during at least one early session and one later session, rating fidelity and providing coaching to the leaders. After these initial peer groups are completed, the peer leaders and committee will meet to reflect on lessons learned and prepare for future implementation. The lessons learned from both rounds of groups will be shared with implementation partners and iteratively used to modify the 3-Step Model. *The primary capacities built during this period are: experience in using the* 3-Step Model *and offering Mzake, practical logistics for local implementation and completing the benchmarks self-evaluation for committee members.*

*Sustaining* is divided into two periods, 11 months of sustaining with partial support, followed by independent sustaining up to the last year of the grant period. Because of the staggered implementation plan, Site 1 will have 30 months of independent sustaining, Site 2 will have 18 months and Site 3 will have 8 months of independent sustaining. During sustaining with support, sites are told that they will receive a specific amount of money for 11 months of sustaining activities. The committee members receive advanced training regarding sustaining and discuss their vision for what should happen. They receive additional guidance on planning activities, budgeting for them and accounting for expenditures. Activities during sustaining include training more peer group leaders and possibly new committee members, holding *Mzake* groups for new participants and in new areas, and booster activities for those who have already attended *Mzake*. One important part of sustaining is ensuring the capacity to train new peer group leaders, and the committee may decide to ask for training of interested peer leaders as trainers. They then decide how to allocate their efforts and carry out their plans, monitoring what is happening and making any needed adjustments. Toward the end of sustaining with support, the committee learns how to write a proposal and budget in a workshop and seeks funding from us and other sources. Our staff is available but does not initiate regular contacts as we do during roll-out.

During independent sustaining, the community should begin to expand to new areas and obtain new support for their work. They can apply to us for a small grant and to the District Commissioner’s office and other funders for additional months of partial funding. The Study Team continues “hands-off” observation of progress during the remainder of this period [23]. The intention is for each community to continue indefinitely. However, we only observe progress up to Month 52. *The primary capacities built during this period are independently training new peer leaders, conducting booster sessions, expanding to new parts of their own site and possibly to other sites, maintaining financial records, and preparing proposals and budgets to sustain activities.*

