## Methods

### Design

This study uses a hybrid design, which was developed to advance implementation science by examining both implementation processes and effectiveness in a single study [25, 26]. We give equal attention to both processes and effectiveness evaluation, a balanced design recommended where there is already evidence supporting efficacy [25].

We use a stepped wedge design to evaluate effectiveness, with staggered introduction of the intervention in three communities in randomly assigned order (Fig. 1). The stepped wedge design [27–29] has the advantage that all groups receive the intervention, which is ethically important, especially in a community intervention. This design is efficient because the repeated measures allow participants to serve as controls until the intervention is introduced in their community. In each community, the first 144 adults and 144 youth are asked to both receive the intervention and to participate in the effectiveness evaluation. Outcome measures are assessed at baseline and after each community rolls out the intervention.

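### The Sustain step encourages Site 1 to expand into new areas while Site 3 is the only control, and no stated rule beyond participant residence keeps that expansion out of Site 3

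*Protocol article*

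**What the plan says.** Under Design, the wedge relies on the fact that "repeated measures allow participants to serve as controls until the intervention is introduced in their community". The Aim 3 hypothesis likewise compares people who completed the programme with communities where it has not yet been introduced. Surveys are taken at baseline and after each community's roll-out.

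Under Setting and sample, all three sites come from one sub-district area: "The leaders in that area selected three communities as sites for implementation". Community participants must live in the designated community.

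Under Implementation at 3 sites, Sustain consists of "11 months of sustaining with partial support, followed by independent sustaining". The activities listed for Sustain include "groups for new participants and in new areas, and booster activities for those who have already attended". The committees decide how to use their effort, and staff do not initiate regular contact. The paragraph on independent sustaining urges expansion to new areas and ends with a list of capacities that includes "expanding to new parts of their own site and possibly to other sites". The stagger between sites can be read from this statement: "Site 1 will have 30 months of independent sustaining, Site 2 will have 18 months and Site 3 will have 8 months".

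The survey (Table 1) records the date of the last session and the number of sessions attended. The Aim 3 analysis codes intervention condition by the stepped-wedge schedule.

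**The concern.** A stepped wedge needs the waiting community to stay unexposed until its own start. Here the early communities are funded and encouraged to recruit new people in new places during the period when the last community supplies the only concurrent control data. If some of Site 3's cohort attend groups run by Site 1, or take up its messages, they are still coded as control at Wave 3. That raises the control level and removes part of Site 3's own before-after change.

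Provided early exposure acts in the same direction as the programme itself, the bias is toward no effect. It also grows with the success of sustaining, which is the other half of a hybrid design meant to give both halves equal attention.

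**Working it through.** **Timeline** (month 0 = start of Site 1's Prepare)

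Inputs from Implementation at 3 sites: Prepare 2 months, Roll-Out 8, supported sustaining 11, and independent sustaining of 30, 18 and 8 months for Sites 1, 2 and 3. If observation ends at the same time everywhere, Site 2 starts 30 − 18 = 12 months after Site 1, and Site 3 starts 18 − 8 = 10 months after Site 2, which is month 22. The alternative is back-to-back sites, starting at months 0, 10 and 20.

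| Event | Stagger from 30/18/8 | Back-to-back |
|---|---|---|
| Site 1 enters Sustain (2 + 8) | 10 | 10 |
| Site 1 independent sustaining (10 + 11) | 21 | 21 |
| Site 2 roll-out ends, Wave 3 due | 12 + 10 = 22 | 10 + 10 = 20 |
| Site 3 roll-out begins | 22 + 2 = 24 | 20 + 2 = 22 |

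So Site 1 is in Sustain for 10 to 12 months before Wave 3. The independent period, where other sites are mentioned, starts at most 1 month before Wave 3 and 1 to 3 months before Site 3's roll-out. Site 2 enters Sustain only at about the time of Wave 3. Wave 2 falls at about month 10, before any Sustain activity, so the control cell at risk is Site 3 at Wave 3. Only differences between sites are used, so calendar months do not matter.

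**Which model?** The article gives no figure for spread. The nearest figure is the minimum detectable effect of 0.13 under Power analysis. A generalised least-squares calculation used 144 per site, cluster ICC 0.10, individual ICC 0.2 to 0.4, the stated retention and an assumed two-sided 5% level. It gives 0.115 to 0.144 without a wave term, which covers 0.13, and 0.195 to 0.250 with one. The Aim 3 analysis does not settle whether a wave term is included, so both cases follow.

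**Weight of the Site 3, Wave 3 cell.** Exposure by wave is 0,1,1,1 in Site 1, 0,0,1,1 in Site 2 and 0,0,0,1 in Site 3. With r the exposure left after adjustment, the cell's weight is r / Σr². If the cell carries a fraction c of the full effect, the estimate is multiplied by 1 + c × weight.

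- *Site and categorical wave:* r = 0 − 0.25 − 0.6667 + 0.5 = −0.4167. Σr² = 0.3056 + 0.2222 + 0.3056 = 0.8333. Weight = −0.50.
- *Site only:* r = 0 − 0.25 = −0.25. Σr² = 0.75 + 1.00 + 0.75 = 2.50. Weight = −0.10.

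| Assumed c | Multiplier, wave effects | Multiplier, no wave effect |
|---|---|---|
| 10% | 1 − 0.05 = 0.95 | 1 − 0.01 = 0.99 |
| 20% | 1 − 0.10 = 0.90 | 1 − 0.02 = 0.98 |

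The mixed-model calculation with the stated retention, individual ICC 0.3 and 12 peer groups per site agrees: 0.951 and 0.903 with wave effects, 0.991 and 0.981 without. Starting from 80% power in each model, power becomes 76.0% and 71.5% with wave effects, and 79.2% and 78.5% without.

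**The case against.** **New areas need not mean Site 3.** The sub-district is the largest in the district and holds a third of nearly 350,000 people, so a little under 117,000. No distances or boundaries are given, and the article speaks of new parts of a community's own site. This stands as a limit on likelihood: being in one sub-district does not show adjacency. It does not supply a rule.

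**Other sites come late.** A reader might infer that Site 1 is sent to other sites throughout the months when Site 3 is the control. The text does not support that. The phrase belongs to independent sustaining, overlaps the run-up to Wave 3 by 0 to 1 month, and may mean communities outside the study. What covers the whole of Sustain is new participants and new areas.

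**There is some restraint.** The residence criterion weighs against Site 1 enrolling Site 3 residents, so it would be wrong to say that nothing stands in the way. It does not govern where groups are held.

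**The cohort is closed.** The evaluation cohort is recruited at Wave 1, so direct contamination requires those particular people to attend another community's groups. This is fair. They are, however, people already willing to join, who then wait about two years.

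**Exposure is already measured.** A reader might infer that the survey misses early attendance. In fact the procedure is the same at each wave, and nothing restricts the attendance items to started communities. The gap is only that no use of them for early exposure is stated, and that detail could sit in an analysis plan.

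**The guide is not shown.** The coordinating committee's guide may already limit expansion. That cannot be excluded. Still, the article itself promotes expansion without excepting the waiting communities on which its control definition depends.

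**Conclusion.** The point holds as a gap in the design: the plan promotes an activity that can breach its own definition of control, in the one cell that supplies the concurrent control at Wave 3. The timing follows from the stated durations under either reading of the stagger.

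The size does not follow from the documents. The 10% and 20% levels of spread are assumptions. A reader might take the 5% to 10% loss as the expected bias, but it also needs categorical wave effects, which the Aim 3 analysis does not specify. Without a wave effect the loss is about 1% to 2%. The article shows neither that contamination will happen nor that it would be large. It shows that a foreseeable bias toward no effect has only a partial safeguard. This is a cheap improvement worth making, because contamination cannot be undone later. When the article was written, two of the three communities had begun roll-out, so Site 3 could still be protected.

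**What to change.** Add one rule to the Sustain step and to the coordinating committee's guide. Until the Wave 3 survey is finished in Site 3, groups run by other study communities are not held in the villages of a study community that is still waiting, and do not enrol its residents. All other new areas stay open.

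For the analysis, use the sessions-attended and last-session items already collected at every wave to count early attenders in communities that have not started. Report a sensitivity analysis that codes them as exposed. Keep schedule-based coding as the main analysis, because early attenders choose to attend and differ from others for that reason. The items will not capture messages passed on informally, so the geographic rule is the main protection.

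The cost is a sentence in two places, one extra analysis and a temporary geographic limit on the early communities' expansion. Site 3 still receives the programme on schedule, and no new data are needed.
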